### Ethical Considerations

All components of this study were reviewed for ethical compliance by the Queen’s University Health Sciences and Affiliated Teaching Hospitals Research Ethics Board (File #: 6033212) in April 2022. Participants are only identifiable by an ID number, and all records are stored on a secure platform. Participant data is only accessible by the care providers, and anonymized data is provided to the analysis team. Participants can withdraw from the study at any point and request that their data be removed from the analysis. The research team will safeguard the privacy of the participants to the extent permitted by the applicable laws and their duty to report.

OPTT is compliant with the Health Insurance Portability and Accountability Act, Personal Information Protection and Electronic Documents Act, and Service Organization Control 2. All servers and databases are hosted in Amazon Web Service Canada cloud infrastructure to assure provincial and federal privacy and security regulations are met. OPTT does not collect identifiable personal information or IP addresses. OPTT collects anonymized metadata to improve service quality and provide advanced analytics to the clinician team.

### Data Analysis

The data will be initially assessed for outliers, missing, and nonsensical variables. These variables will not be imputed, since they will be handled as missing. Similar studies that involved CBT and e-CBT demonstrated a dropout rate of up to 40% for both conditions once the study concluded [49]. Thus, this study will intentionally oversample the experimental and control groups to account for this dropout rate. Considering the effect size for face-to-face RPT reported by Harada et al [50] (2021) for CBI (effect size=0.65), a significance level of α=.05 and a power of 0.90, a sample size of 60 (30 per arm) would be sufficient to detect substantial changes from our interventions [51]. As this is the first study aiming to establish an e-RPT program for AUD, this sample size calculation relies on data from face-to-face RPT and takes into account the established effectiveness of online psychotherapy compared to face-to-face psychotherapy [30].

The analysis will begin by examining the data for missing, nonsensical, and outlying variables. The data will then be analyzed on a per-protocol basis, excluding missing data, and with intention-to-treat analysis to assess the clinical effects of the program on participants who dropped out prematurely. All calculations will be done using a 2-tailed significance level of α=.05, except for when a Bonferroni correction is needed. The demographic information of program completers and program dropouts will be compared using independent sample *t* tests to identify possible differences. A 2 by 3 repeated measures ANOVA of the primary (daily drinking and relapse) and secondary (SCQ-100, Q-LES-Q-SF, RS-14, CBI, and PHQ-9) outcomes will be conducted to test for the effects of the interventions (e-RPT or face-to-face RPT) throughout the 10-week treatment (0, 5, and 10-week assessment points). Linear regression (for continuous outcomes) and binomial regression analysis (for categorical outcomes) will be used to identify variables associated with outcome measures. Additionally, OPTT will collect usage statistics (ie, number of logins per day, amount of time spent logged in) and compare them to face-to-face metrics (ie, attendance to weekly 1-hour face-to-face sessions) to determine cost and time savings between the 2 programs. All statistical analyses will be conducted using IBM SPSS Statistics for Mac (version 24; IBM Corp).

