Participant inclusion criteria are being 18 years or older at the start of the study and having a diagnosis of mild to moderate AUD according to the MINI (2 to 5 MINI AUD symptom criteria) [20], competence to consent and participation, ability to speak and read English, and consistent and reliable access to the internet. Additionally, contemplation about stopping or having stopped consuming alcohol in the past 30 days is required. This will be assessed by the RCQ (participants should be in the contemplation or action stage according to the questionnaire) and by asking them about when they stopped drinking or began considering alcohol cessation [34,35]. Exclusion criteria are acute hypomanic or manic episodes, acute psychosis, other active substance use disorders classified as moderate or severe, active suicidal or homicidal ideation, untreated clinically substantial somatic symptoms or mental disorders, or current enrollment in another relapse prevention program. Additionally, men who consumed more than 4 drinks per day or 14 drinks per week and women who drank 3 drinks per day or 7 drinks per week in the past month will be excluded [36].

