### Outcome Measures

The primary objective of this study will be to determine if e-RPT has similar effectiveness to face-to-face RPT at reducing alcohol consumption and preventing relapses. This study defines relapse as either the consumption of at least 2.5 oz. of pure ethanol, which is around 4 and a half standard drinks (Canadian guidelines for standard drinks: 12 oz of beer with 5% ethanol, 12 oz of cider with 5% ethanol, 5 oz of wine with 12% ethanol, and 1.5 oz of spirits with 40% ethanol) [41,42] on one occasion or hospitalization because of alcohol drinking [43]. Therefore, to determine the effectiveness of this program, daily alcohol consumption will be recorded in a drinking diary accessible through OPTT. This diary will ask the participants to report how many drinks they consumed on each day of the week, where they had those drinks, with whom, and if their alcohol consumption resulted in hospitalization (Figure 1).

The study will also determine whether e-RPT and face-to-face RPT have a beneficial effect on self-efficacy, quality of life, resiliency, coping behaviors, and depressive symptomatology. These metrics will be assessed through the following scales: Situational Confidence Questionnaire (SCQ-100) [44], 14-item Resilience Scale (RS-14) [45], Coping Behaviors Inventory (CBI) [46], Patient Health Questionnaire (PHQ-9) [47], and Quality of Life Enjoyment and Satisfaction Questionnaire—Short Form (Q-LES-Q-SF) [48]. These assessment scales will be completed at study entry (baseline), amid the program (week 5), and post treatment (week 10). After the treatment period, we will conduct follow-up assessments with all our outcome measures at 3, 6, and 12 months. The amount of time that e-RPT therapists spend writing feedback compared to the 1-hour face-to-face session will be used as a measure of therapists’ time efficiency and will be tracked on the OPTT platform.

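### Outliers are to be handled as missing with no exemption for the drinking diary, so genuine heavy-drinking values and relapse events can be removed from the primary outcomes

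*Protocol article*

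**What the plan says.** The rule stands at the start of the Data Analysis section of the protocol article: "The data will be initially assessed for outliers, missing, and nonsensical variables. These variables will not be imputed, since they will be handled as missing". The next paragraph makes the same screen the first step of the analysis: "The analysis will begin by examining the data for missing, nonsensical, and outlying variables". The analyses then follow, per protocol without missing data and by intention to treat. No outlier criterion is given, and no variable is exempted.

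The primary outcomes in that section are daily drinking and relapse. Under Outcome Measures, "daily alcohol consumption will be recorded in a drinking diary accessible through OPTT". Relapse is the "consumption of at least 2.5 oz. of pure ethanol, which is around 4 and a half standard drinks" "on one occasion or hospitalization because of alcohol drinking".

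Under Study Design and Participants, the exclusions cover "men who consumed more than 4 drinks per day or 14 drinks per week and women who drank 3 drinks per day", with a weekly limit of 7 drinks for women. People who stopped drinking in the past 30 days may enter.

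**The concern.** A screen for outliers normally guards against recording errors. Here the extreme values of the primary variable are what the trial exists to count. Participants enter at low drinking levels, some abstinent, so a day that meets the relapse threshold sits in the upper tail of the diary counts. A rule that turns outlying values into missing values can then turn relapses into missing data.

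Such values would be missing because they are high, which is missingness not at random. Neither analysis set, as described, restores them: one leaves missing data out, and the other is presented as addressing people who drop out, with no imputation. The study hypothesises similar effectiveness, so an error that can shrink the absolute difference between arms works in favour of the expected conclusion.

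**Working it through.** **1. Relapse threshold in drinks.** The article's drink sizes give 12 oz × 5% = 5 oz × 12% = 1.5 oz × 40% = 0.6 oz of ethanol. The threshold is 2.5 / 0.6 = 4.17 drinks, against about 4.5 as stated. The two figures should be reconciled, but in whole drinks both mean a day of 5 or more.

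**2. Where that lies relative to entry drinking.** The weekly limits correspond to 14 / 7 = 2 drinks per day for men and 7 / 7 = 1 for women. The daily limits are 4 and 3. Whether these are read as averages or maxima, 5 drinks is above all of them.

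**3. Share of days with 5+ drinks that a common rule would flag.** The article gives no cut-off or distribution, so this step is assumption. Take single days as the unit and negative-binomial counts with mean μ and variance μ + μ²/k. The rules are Q3 + 1.5 × IQR and mean + 3 SD.

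| μ | k | IQR fence | 5+ days flagged | mean + 3 SD | 5+ days flagged |
|---|---|---|---|---|---|
| 0.5 | 0.5 | 1 + 1.5 = 2.5 | 100% | 0.5 + 3 × 1.00 = 3.5 | 100% |
| 1 | 0.5 | 1 + 1.5 = 2.5 | 100% | 1 + 3 × 1.73 = 6.2 | 39% |
| 1 | 1 | 2.5 or 5 | 100% or 50% | 1 + 3 × 1.41 = 5.2 | 50% |
| 2 | 1 | 3 + 4.5 = 7.5 | 30% | 2 + 3 × 2.45 = 9.3 | 13% |
| 2 | 2 | 7.5 or 6 | 18% or 32% | 2 + 3 × 2 = 8 | 10% or 18% |

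The double entries are ties. With μ = 1, k = 1, exactly 75% of days have 0 or 1 drink, so Q3 falls at 1 or 2 by chance. With μ = 2, k = 2, exactly 25% of days are zero, so Q1 is 0 or 1, and mean + 3 SD is exactly 8. No narrower figure is meaningful there.

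Example for μ = 2, k = 1: P(X ≥ n) = (2/3)ⁿ. A fence at 7.5 flags 8 or more, a share of (2/3)⁸ / (2/3)⁵ = (2/3)³ = 30%.

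**4. A second day-level model.** A simulation took 60 persons × 70 diary days, with 30–80% of persons ever relapsing, relapse days 2–20% of their days, 5 + Poisson(2) drinks on a relapse day, and 1–3 drinks on 5–40% of other days.

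| Rule | Relapse days flagged, when 2% of days | Whole grid |
|---|---|---|
| beyond 3 SD | 95–100% | 6–100% |
| 1.5 × IQR | 87–100% | 34–100% |
| 3 × IQR | 14–100% | 1–100% |

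Where other drinking falls on only 5% of days, Q1 = Q3 = 0 and both IQR rules flag every relapse day.

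**5. Days are not persons.** Someone with m relapse days loses relapse status only if all are flagged. If each is flagged independently with probability f, that probability is fᵐ: for f = 0.5 it is 50% at m = 1 and 0.5³ = 12.5% at m = 3. For f = 1 it is 100% at any m. In the simulation with 60% relapsers, relapse days at 10% and other drinking on 40% of days, the 3 SD rule flags 54% of relapse days but 4% of relapsers lose status. For 1.5 × IQR the figures are 86% and 38%.

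**6. A different unit.** The planned 2 by 3 ANOVA uses three time points, so one value per person per time point might be screened. Using the μ and k of step 3 as variation between 60 persons and screening weekly means, the share flagged among persons with a 5+ day that week averages 4–55% under 3 SD and 11–88% under 1.5 × IQR.

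**7. Effect on the comparison.** With true event rates a and b and the same share f lost in both arms, the difference becomes (1 − f)(a − b), while the ratio (1 − f)a / (1 − f)b = a / b is unchanged.

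**The case against.** The strongest reply is that the loss is conditional. The screen must act on diary counts or summaries of them, its cut-off must catch relapse-level values, and relapse must be derived after cleaning. The article settles none of these, and the outlier criterion could sit in a fuller protocol or analysis plan that is not shown. This stands as a limit on size. It does not remove the point, because the article does fix what happens to an outlier once identified, and a later cut-off would not change that.

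The sentence might also be read as saying only that missing values are not imputed. But its reference is to all three listed categories, and values already missing need no rule to be handled as missing. If the narrower sense was meant, the sentence still needs correcting.

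A reader might infer that the rule necessarily deletes relapses, or that 5 drinks is always an outlier. The documents do not support this. The Introduction cites relapse in 60% to 80% of people at 3 months, and where heavy days are common far fewer are flagged. Hospitalisation is asked about separately in the diary and is not a drink count. A person with several relapse days may keep relapse status.

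A reader might also infer a sure bias towards similarity. That holds for absolute differences under equal proportional loss, but not for ratios, and with unequal loss the direction is not determined. Setting a value to missing is also not the same as scoring no relapse: a missing time point can drop the whole person from a repeated-measures ANOVA. That too would remove high drinkers, but by another route.

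**Conclusion.** The point holds as a defect in a stated rule. Outliers are to be handled as missing, the primary endpoint rests mainly on high values of a screened variable, and there is no safeguard. The rule can remove genuine heavy-drinking values and relapse events, lowering apparent consumption and relapse and possibly shrinking the absolute difference between arms.

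The size is not determined by the document. At day level, under the assumed distributions and rules, it ranges from about 1% to all relapse-level days. It is high when such days are rare and low when they are frequent and the cut-off is lenient. Loss of relapse status by person is smaller unless every relapse day is flagged. If relapse is derived from the raw diary before cleaning, relapse is untouched and only the consumption outcome remains exposed.

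**What to change.** Replace the sentence so that only verified impossible or erroneous entries become missing, such as negative or non-numeric values or errors confirmed by query. State that relapse is derived from the raw diary before any cleaning, and that all plausible high drink counts and scale scores stay in the main analysis. Any transformation, winsorising or exclusion of extreme values belongs in a sensitivity analysis that never changes relapse status.

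This costs a sentence or two in the protocol or analysis plan, with no change to recruitment, visits or data collection. It should be settled before any diary data are cleaned.

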## Methods

### Study Design and Participants

This is the protocol for a randomized controlled trial studying the efficacy of a novel e-RPT program. Participants (n=60) diagnosed with AUD will be recruited through physician referrals from Kingston Health Sciences Centre, family physicians, other health care providers, and self-referrals within Kingston, Ontario. After providing consent to participate in the study, a Mini International Neuropsychiatric Interview 7.0.2 (MINI) will be conducted to confirm the diagnosis of mild to moderate AUD [35]. The MINI is a diagnostic interview that assesses 17 common mental disorders by following the diagnostic criteria of the *Diagnostic and Statistical Manual of Mental Disorders*, Fifth edition [35]. After the MINI, the Readiness to Change Questionnaire (RCQ) will be administered in an interview format to investigate the individual's desire to change their alcohol consumption [33]. In addition to the RCQ, participants will be asked questions listed in Textbox 1 to capture their history with AUD. Answers to these questions, along with the intake MINI, will be reviewed with the principal investigator (PI) to ensure that the participant meets eligibility criteria and to confirm the AUD diagnosis.

The 6 additional interview questions to establish eligibility.Have you been diagnosed with alcohol use disorder (AUD)?If applicable, when were you diagnosed with AUD?Are you currently enrolled in another relapse prevention program?In the past month, how many times have you had an alcoholic beverage?If applicable, how many drinks did you have on average in those times?If applicable, how many drinks did you have per week on average in the past month?

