The strengths of this program and this study include the use of asynchronous psychotherapy through predesigned web-based modules. These web-based modules have been shown to increase therapy efficiency by allowing a web-based therapist to deliver care to 3 to 4 patients at a time compared to 1 synchronous session [30,39,40]. The use of a web-based platform like OPTT allows for the automatic and reliable collection of user analytics, which can then be used to continuously improve and optimize the delivery of web-based psychotherapy programs. Given that face-to-face RPT has been previously validated in the literature, this study hypothesizes that e-RPT will be effective at maintaining abstinence, reducing the risk of relapse and depression symptomatology, and improving quality of life, resiliency, and coping behaviors [12,24,31,32,50]. Furthermore, comparing our proposed e-RPT program to a validated face-to-face therapeutic approach (RPT) strengthens the design of this RCT and the conclusions that will stem from this evidence.

Despite the strengths of this program, the web-based mode of delivery of this program may have some potential limitations. The main limitation is that participation requires a reliable internet connection and sufficient technology literacy. This limitation could introduce biases in participant demographic characteristics. Thus, this study will analyze demographic factors through multiple sample *t* tests to determine if these factors could impact treatment outcomes. Additionally, due to the delivery mode and design of the program, it is not possible to conceal client allocation. Moreover, web-based psychotherapy is often characterized by a dropout rate of up to 40% by the end of the treatment [49,50]. To account for this without compromising statistical power, this study is intentionally oversampled.

The knowledge dissemination plan for this study includes publishing the outcomes of this study in a peer-reviewed, academic journal. The research team will also attend academic meetings and conferences to present these findings and commit to continuing education in the relevant research areas. Furthermore, the dissemination and application of knowledge will be further enhanced through the collaboration of the Canadian enterprise, OPTT Inc. Additionally, by providing this service to clinicians, the care capacity for accessible, affordable, and high-quality mental health care could be more rapidly scaled across Canada.

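### The claim that oversampling protects power against 40% dropout is not supported by the stated sample-size inputs

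*Protocol article*

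**What the plan says.** The Data Analysis section of the protocol article cites similar studies with dropout of up to 40% in both conditions, and continues: "Thus, this study will intentionally oversample the experimental and control groups to account for this dropout rate". The next sentence takes an effect size from an earlier study of face-to-face RPT, "for CBI (effect size=0.65"), and concludes: "a significance level of α=.05 and a power of 0.90, a sample size of 60 (30 per arm) would be sufficient". The sentence goes on to say what the number is sufficient for, namely detecting substantial changes from the interventions. Neither sentence gives an evaluable number, an inflation factor or the test assumed.

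The enrolment target is the same number. Study Design and Participants says "Participants (n=60) diagnosed with AUD will be recruited", the Abstract gives n=60, and the Procedure section splits them 30 and 30.

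The Discussion returns to the 40% and says: "To account for this without compromising statistical power, this study is intentionally oversampled".

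On analysis, the Data Analysis section rules out imputation, plans both per-protocol and intention-to-treat analyses, sets two-sided testing ("All calculations will be done using a 2-tailed significance level of α=.05"), and names a 2 by 3 repeated measures ANOVA over weeks 0, 5 and 10.

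**The concern.** The number derived from effect size, α and power equals the number enrolled. On the face of the text, nothing has been added for dropout, although the article says twice that something has.

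This matters because the hypothesis is that the two forms of delivery perform similarly, while the tests are two-sided tests of difference. A non-significant comparison is the hoped-for result. If readers believe that 0.90 power survives the expected attrition, they may take such a result as evidence of similarity when the trial could easily have missed a difference of the assumed size.

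**Working it through.** **Inputs.** Effect size 0.65, α=.05, power 0.90, 60 enrolled (30 per arm) and dropout of up to 40%, all from the sections cited above. Two-sided testing is from Data Analysis. The article does not say what kind of effect size 0.65 is; here it is taken as a standardised mean difference d, either between arms or within an arm.

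**Step 1: reproduce the stated size.** Power comes from the noncentral t distribution. For two arms the noncentrality is d√(n/2) with 2n−2 degrees of freedom. For a within-arm (paired) change it is d√n with n−1 degrees of freedom.

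| Reading of 0.65 | Evaluable n per arm for 0.90 | Enrolled per arm after 40% loss |
|---|---|---|
| Difference between two arms | 51 | 51/0.6 = 85 |
| Pre-post change within one arm | 27 | 27/0.6 = 45 |

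Neither reading gives 30 per arm, before or after inflation. One-sided testing does not either: about 42 per arm for two arms and 22 for a paired change. The nearest is the two-sided paired calculation, for which 30 per arm leaves room for a loss of 1 − 27/30 = 10%, not 40%.

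**Step 2: apply the stated dropout.** 30 × (1 − 0.4) = 18 per arm; 60 × 0.6 = 36 in total.

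**Step 3: power for d=0.65, two-sided .05.**

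| Reading | Noncentrality at n=18 | Power at 30 per arm | Power at 18 per arm | Detectable d at 0.90 power, 18 per arm |
|---|---|---|---|---|
| Between arms | 0.65 × √9 = 1.95 | 0.70 | 0.47 | 1.11 |
| Within one arm | 0.65 × √18 = 2.76 | 0.93 | 0.74 | 0.81 |

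The between-arm reading falls short of 0.90 even with no dropout. The within-arm reading meets it with no dropout and loses it at 18.

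**Step 4: look for readings on which 36 completers do give 0.90.**

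- *Pre-post change pooled over both arms.* Paired t test, n=36: power 0.97, with 27 needed in total. This does not compare the arms.
- *The planned ANOVA* (2 groups, 3 times, 36 completers), assuming a conversion to f = 0.65/2 = 0.325 and a common within-person correlation ρ. The article gives neither. Noncentrality is f²·N·3/(1+2ρ) for the between-arm effect and f²·N·3/(1−ρ) for time or group-by-time; at ρ=0 both equal 0.325² × 36 × 3 = 11.41.

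| ρ | Between-arm main effect | Time or group-by-time |
|---|---|---|
| 0 | 0.91 | 0.85 |
| 0.2 | 0.79 | 0.92 |
| 0.3 | 0.74 | 0.95 |
| 0.5 | 0.64 | 0.99 |

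The between-arm effect reaches 0.90 with essentially uncorrelated repeated measures. The time and group-by-time effects reach it at ρ of about 0.2 or more, provided that f=0.325 is the right size for those effects.

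**The case against.** The strongest reply is that 60 may already include the allowance. The article mentions the 40% first, says that it will oversample, and only then gives 60. That order can be read as 36 evaluable inflated to 60, and nothing in the text calls 60 the size before inflation. One ANOVA route fits this exactly: the between-arm effect with f=0.325 and zero correlation needs 36, and 36/0.6 = 60. The t tests are also not the planned analysis, and the group-by-time effect, which does compare the arms, can reach 0.90 with 36 completers.

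This stands in part. A reader might infer that 60 is an unadjusted size and that the protection therefore does not exist. The article does not support going that far: it never says which side of the inflation 60 is on, no t-test reading yields 30 per arm, and the ANOVA routes above cannot be excluded.

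It does not rescue the claim. If 60 is already inflated, both per-arm t-test readings still fall short at 36 completers. The ANOVA routes need a conversion, a correlation and a target effect that the article does not supply, and the between-arm route fails once repeated measures are even modestly correlated.

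Two further defences are weaker. A condensed article may leave detail to a fuller document, but here it asserts a property twice and its own inputs do not yield it. The planned intention-to-treat analysis does not restore the lost data either, because imputation is ruled out and a standard repeated measures ANOVA uses complete cases.

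**Conclusion.** The concern holds in this form: the statements that the arms are oversampled and that power survives 40% dropout are not supported by the stated inputs. Under the article's own dropout figure, 36 participants (18 per arm) are evaluable. Power for 0.65 is then 0.47 between arms or 0.74 within an arm, against the stated 0.90. These powers assume that 0.65 is a standardised mean difference, that testing is two-sided at .05, that the full 40% is lost equally from both arms, and that those lost contribute nothing to the analysis.

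What is not shown is that 0.90 is unattainable with 36 completers. It is attainable for a pooled pre-post change, and for the planned ANOVA under assumptions that the authors would have to state and defend.

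**What to change.** In the sample-size paragraph of Data Analysis, state that 60 are enrolled and that about 36 (18 per arm) are expected to be evaluable at week 10 under 40% loss. Give the power, or the effect detectable with 0.90 power, at that number for the planned between-arm test, and name the effect tested, the effect-size conversion and the assumed within-person correlation. The t-test figures can serve as a benchmark: 0.47 (two-arm) and 0.74 (within-arm) for 0.65, or about 1.11 and 0.81 SD at 0.90 power.

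Withdraw the oversampling statement there and the matching sentence in the Discussion, unless that calculation shows that 36 completers give 0.90.

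The cost is one rewritten paragraph, one Discussion sentence and, probably, a less favourable stated power. No additional enrolment or change of design is needed.

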### Procedure

Upon completion of the eligibility assessments, participants will be randomly assigned through a computerized system to one of the 2 groups: e-RPT or face-to-face RPT. Participants will be equally stratified (e-RPT n=30; face-to-face RPT n=30). These treatments will be delivered as an augmentation to treatment as usual (eg, medications, regular physician or clinician visits, referrals, or consultations that are conducted outside of this research study). The e-RPT program will be delivered through the Online Psychotherapy Tool (OPTT), a secure and interactive platform developed by the PI [37]. The face-to-face RPT program will be delivered through videoconference sessions using Microsoft Teams. Participants in the e-RPT and face-to-face groups will also have access to OPTT to access the triage module, the daily drinking diary (Figure 1), and assessment questionnaires.

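### The Data Analysis section describes the intention-to-treat analysis as being about dropouts, lists per-protocol first, and does not say which set decides the primary comparison

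*Protocol article*

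**What the plan says.** All of this is in the protocol article.

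- **Data Analysis, the two sets.** "The data will then be analyzed on a per-protocol basis, excluding missing data, and with intention-to-treat analysis to assess the clinical effects". Per-protocol comes first. The rest of the sentence gives ITT its purpose: "with intention-to-treat analysis to assess the clinical effects of the program on participants who dropped out prematurely".
- **Data Analysis, significance level.** "All calculations will be done using a 2-tailed significance level of α=.05, except for when a Bonferroni correction is needed". No family of tests is named for the correction, and it is not linked to the two analysis sets.
- **Data Analysis, primary test.** A 2 by 3 repeated measures ANOVA is named for the primary and secondary outcomes. It is not tied to either set. Missing values are not imputed.
- **Data Analysis, expected loss.** Similar studies "demonstrated a dropout rate of up to 40% for both conditions once the study concluded".
- **Outcome Measures, aim.** "The primary objective of this study will be to determine if e-RPT has similar effectiveness to face-to-face RPT". No margin for similarity is given.
- **Procedure, allocation.** "Participants will be equally stratified (e-RPT n=30; face-to-face RPT n=30".

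The article does not say which set decides the primary comparison, or what is concluded if the two sets differ.

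**The concern.** ITT is the comparison that randomisation protects, and its purpose is to estimate the difference between arms in everyone randomised. Describing it as a way to learn about people who dropped out turns it into a side analysis and leaves the per-protocol comparison looking like the main one. Completers are selected after randomisation. The article itself plans to compare completers with dropouts, so it recognises that they may differ.

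Two things are at stake:

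- **A claim of difference.** If either set may support it, the error rate is above the nominal 0.05.
- **A claim of similarity.** The sponsor expects the arms to be similar. The smaller per-protocol set is the one more likely to give a non-significant result, and such a result could be read as confirming that expectation.

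**Working it through.** The plan states no figure on this point to reproduce, so the check measures what an unranked pair of sets could do.

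**Inputs from the article.** 30 per arm (Procedure); dropout up to 40% in both conditions, two-sided α = .05 (Data Analysis).

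**Assumptions that are not in the article.** ITT has an outcome for all 60; dropout is random; there is one primary test; test statistics are approximately normal; no correction is applied across the two sets. For the disagreement figures, the ITT statistic has mean 2.0, which gives ITT power of about 52%.

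**Step 1: correlation of the two tests.** Let a share s complete in each arm. The per-protocol set is a subset of the ITT set. The covariance of the full and subset means is σ²/n, and their variances are σ²/n and σ²/(ns). Hence r = (1/n) / √[(1/n)(1/(ns))] = √s. At 40% dropout, 18 of 30 per arm complete and r = √0.6 = 0.775.

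**Step 2: type I error under free choice.** With no arm difference, P(at least one significant) = 1 − P(|Z₁| < 1.96 and |Z₂| < 1.96), from a bivariate normal with correlation r.

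**Step 3: disagreement when a difference exists.** The means are 2.0 for ITT and 2.0·√s for per-protocol. P(disagree) = P₁ + P₂ − 2·P(both significant). At 40% dropout this is 0.516 + 0.341 − 2 × 0.300 = 0.257. At 10% it is 0.516 + 0.475 − 2 × 0.442 = 0.107.

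| Dropout | Completers per arm | r | P(either significant), no difference | Per-protocol power | Sets disagree |
|---|---|---|---|---|---|
| 10% | 27 | 0.949 | 0.065 | 0.48 | 11% |
| 20% | 24 | 0.894 | 0.071 | 0.43 | 16% |
| 30% | 21 | 0.837 | 0.076 | 0.39 | 21% |
| 40% | 18 | 0.775 | 0.080 | 0.34 | 26% |

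**Step 4: cross-checks.** A simulation of t tests with 30 per arm and an 18-per-arm subset (100,000 runs) gives 0.081 for the null case at 40% dropout. Two independent tests would give 1 − 0.95² = 0.0975; the overlap of the sets keeps the inflation below that.

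**Step 5: the similarity side.** Take the article's effect size of 0.65 (stated for the CBI, read here as SD units) as a true difference between arms. The chance of a non-significant t test is then 30% with 30 per arm and 53% with 18 per arm. In the same simulation at least one set is non-significant in 56% of trials and the sets disagree in 28%. ITT power is about 70% here, so the disagreement figure depends only mildly on the power assumed in Step 3.

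**Step 6: the plan as written.** Without imputation, a standard repeated measures ANOVA drops anyone with a missing time point. An ITT analysis run that way could lose many of the same people as the per-protocol analysis. As the sets converge, r moves towards 1 and the values in the table fall towards 0.05 and 0%.

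**The case against.** **Ranking analysis sets can be left to the SAP.** This is the strongest objection. A journal article condenses the full protocol, and silence on which set is primary would not be a finding by itself. That is fair, but the article is not merely silent. It gives ITT a purpose that is wrong and puts the completer analysis first. That wording needs correcting whatever another document says.

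**Tempting stronger readings.** A reader might infer any of the following, and the documents do not support them:

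- *Both sets are tested at full alpha, so the error rate is 0.080.* The article makes an exception for a Bonferroni correction. Its scope is undefined, so it neither protects against the choice nor allows one to say that no correction will be made. The 0.080 belongs to the 40% dropout limit.
- *Per-protocol is the primary analysis.* The order and the ITT clause suggest it, but the article does not say so. If it were so, the defect would be the wrong primary set, and the free-choice error rate would not apply.
- *The arms will lose different kinds of patients.* This is possible, since participants know their arm and the delivery differs. But the article gives the same dropout limit for both conditions, and nothing in it shows selective loss.

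**Similarity is a margin problem.** Reading non-significance as similarity would remain a fault even with one named set. This stands: ranking the sets does not cure it, and requiring both sets to agree means little without a margin.

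**Conclusion.** The point holds in a limited form. The Data Analysis section misdescribes ITT and leaves open which set decides the primary comparison, so a completer comparison not protected by randomisation could become the main result.

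The numerical effect is moderate: type I error of about 0.065 to at most about 0.080 instead of 0.05, and disagreement between sets in about 11% to 26% of trials, for dropout of 10% to 40%. These figures rest on ITT data for all 60, random dropout, a single primary test, a free choice without correction and, for disagreement, an ITT power of about 52%. They would be smaller if missing data made the sets partly coincide. They do not include any bias from selective dropout, which could be added but cannot be sized from the article.

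**What to change.** In the Data Analysis section, replace the clause on the purpose of ITT with wording to this effect:

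- The comparison of all randomised participants, in their assigned arm, is the primary analysis and decides any claim that the arms differ.
- The per-protocol analysis is a supportive sensitivity analysis and cannot by itself support a claim.
- A conclusion of similar effectiveness must be consistent in both sets and judged by the confidence interval against a prespecified margin, not by a non-significant test. The sponsor must set and justify that margin.

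Because similarity must hold in both sets, that rule needs no extra alpha adjustment. The change needs no new data and should be made before outcomes are seen. Its price is that a favourable result in completers alone can no longer be the headline.
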